## Abstract

**Background:**

Interval training in deep water running (DWR-IT) is a training method to improve cardiovascular fitness, functional health, and quality of life and to help control body weight. Its main advantages are the reduction of joint overload and a low risk of musculoskeletal injuries. The aim of the study is to investigate the influence of DWR-IT on functional capacity, body composition, and quality of life of overweight middle-aged adults.

**Methods:**

This is a randomized controlled, two-arm, open, parallel clinical trial with overweight adults. Volunteers will be allocated to a water group (WG), which will be submitted to the intervention, or a control group, which will not be subjected to any kind of intervention. The evaluation will be composed of anamnesis, electrical bioimpedance, six-minute walk test (6MWT), questionnaire on the Impact of Weight on Quality of Life-lite (IWQOL-LITE), Pittsburgh Sleep Quality Index, Epworth Sleepiness Scale, chair stand test, arm curl test, and food frequency questionnaire. The DWR-IT will last for 12 weeks, systematically increasing the intensity and training volume.

**Discussion:**

The objective of this clinical trial is to evaluate the effect of DWR-IT on overweight adults. The study is guided through practice based on scientific evidence for the use of training and aquatic rehabilitation. It is expected that after 12 weeks of aquatic intervention there will be a decrease in body fat by about 10%, evaluated by electrical bioimpedance, an increase of about 25% of cardiorespiratory endurance, evaluated by 6MWT, and an improvement of about 25% of physical function domains, self-esteem, distress in public places, and work, analyzed by IWQOL-LITE in the WG.

**Trial registration:**

The study protocol was published in the Brazilian Registry of Clinical Trials (ReBEC) on June 16, 2016. Registration number: RBR-6dmh7d.

**Electronic supplementary material:**

The online version of this article (10.1186/s13063-019-3618-7) contains supplementary material, which is available to authorized users.

## Background

Obesity is a serious public health problem in Brazil and worldwide [1]. It has been defined as a chronic disease characterized by the excessive accumulation of body fat in the adipose tissue [2, 3]. Obesity affects 13% of the world’s adult population and if this trend continues, the percentage can reach 20% by 2025 [4]. In Brazil, statistics are also alarming since in 10 years the prevalence rates of overweight have increased [5]. Overweight and obesity are associated with increased morbidity and mortality. Some studies showed that overweight was associated with twice the risk of developing cardiometabolic disease—such as coronary artery disease, cerebral apoplexy, and high blood pressure, and type 2 diabetes mellitus—and other diseases such as endometrial and colorectal cancer, sleep apnea, low self-esteem and eating disorders are also on the rise because of obesity [6].

Obesity and overweight are ewlated to musculoskeletal pain and injury, biomechanical adaptions as a result of the sheer bulk and force of increased fat mass affected locomotion, balance, and strength. Obesity also negatively affects cardiorespiratory function, a fact that promotes the decline of quality of life and sleep and activities of daily living [6–8].

The regular practice of physical activity has been shown to be an efficient strategy to increase energy expenditure and consequently to minimize the effect of excess body weight on quality of life and sleep [6]. Thus, it has been considered a primary component for promoting the physical, functional, psychological, and cognitive health of overweight and obese individuals [7–10]. The American College of Sports Medicine recommend as a component of weight management for prevention of weight gain, for weight loss, a minimum of 150 min-week to 250, 250 min-week of moderate-intensity physical activity [11]. However, it is difficult for an obese person to participate because of increased excessive joint overload, pain, and risk of musculoskeletal injuries [12–14].

Aquatic exercise is highly recommended because of its numerous benefits to the human body through the use of the water’s buoyancy, which can help decrease body fat while maintaining superior stability compared with ground exercises [15]. The deep water running in interval training (DWR-IT) is a new approach in the field of aquatic exercise to control obesity and aims to increase energy expenditure, improve cardiovascular fitness, and reduce body fat percentage [16].

DWR-IT is an aquatic aerobic exercise performed in relatively deep pools and consists of simulated running while wearing a floatation vest, which serves to keep the body in an upright position and helps to prevent contact between the feet and the bottom of the pool [17]. The main advantages of the DWR-IT technique are buoyancy and lack of weight-bearing, minimizing the repeated stress and impact experienced in running on land, and low risk of musculoskeletal injuries. In addition, the individual can perform the same amount of work intermittently and with the same intensity as continuous exercise; however, the degree of fatigue after interval training is considerably smaller and more pleasant for this population [18].

However, little is known about the chronic effects of DWR-IT performed in a heated pool (32 °C), in the body composition evaluated by electrical bioimpedance and functional capacity measured by the six-minute walk test (6MWT) in overweight and middle-aged obese.

Given the above, the proposal of the present study for the advancement of scientific knowledge in the area of aquatic training and rehabilitation in overweight and obese women becomes relevant. Accordingly, the objective of the study will be to investigate the effect of the DWR-IT program on the body composition, functional capacity, and quality of life of overweight adults.

## Methods

The protocol was developed in accordance with the Standard Protocol Items: Recommendations for Interventional Trials (SPIRIT) and Consolidated Standards of Reporting Trials (CONSORT) guidelines and checklists. See Additional file 1 for a SPIRIT checklist and Fig. 1 for the recommended SPIRIT figure.

**Fig. 1 Fig1:**
[figure not shown]
Standard Protocol Items: Recommendations for Interventional Trials (SPIRIT). Information about the selection, recruitment and evaluations carried out in each period. *Abbreviations*: *6MWT* six-minute walk test, *BMI* body mass index, *CG* control group, *ESS* Epworth Sleepiness Scale, *FFQ* food frequency questionnaire, *PSQI* Pittsburgh Sleep Quality Index, *IWQOL-LITE* questionnaire on the Impact of Weight on Quality of Life-lite, *WG* water group

### Overview of research design

This protocol is a two-arm parallel randomized controlled therapeutic clinical trial recruiting overweight and obese volunteers.

### Registry of clinical trials

The study protocol was registered and published in the Brazilian Registry of Clinical Trials (ReBEC) (registration number: RBR-6dmh7d).

### Availability of data and material

Evaluations will be carried out at the Research Laboratory for Physical Therapy, and the intervention program will be held at the Therapeutic Pools Laboratory from the Universidade do Sagrado Coração, Bauru, São Paulo, Brazil. The researcher himself will be responsible for the assessment, reassessment, and supervision of the intervention program.

### Inclusion criteria

Volunteers of both sexes, between 39 and 59 years old (middle-aged), classified as pre-obesity (body mass index (BMI) ≥25 kg/m^2^ to 29.9 kg/m^2^) and obesity (BMI ≥30 kg/m^2^ to 34.9 kg/m^2^) will participate in the study [19]. All volunteers must present a medical prescription attesting the absence of cardiovascular disease that is restrictive to practice the aquatic physical training.

### Exclusion criteria

The exclusion criteria included any history of neuromuscular and cardiorespiratory disease (self-declared) and any contraindications of aquatic physiotherapy: hydrophobia, cutaneous wounds, and infectious diseases [20]. Volunteers may not have participated in another physical training program for at least two months from the beginning of the data collection and may not participate in another training or nutritional monitoring program during the aquatic intervention. For those who use anti-hypertensive drugs and hormone replacement therapy, a change in medication class or dose will not be allowed. As a criterion of adherence after the training period, data from samples that did not obtain at least 80% frequency in the sessions will be excluded.

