### Baseline characteristics

After recruitment and initial screening, details covering demographic data, lifestyle, medications, identification of other diseases, anthropometric assessments, and cardiovascular variables—i.e., blood pressure and heart rate (HR)—will be collected.

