#### Water group (intervention group)

For the DWR-IT program, volunteers will use a Deep Runner vest (Floty^®^, Indaiatuba, SP, Brazil) and cardiac frequency meter (Polar^®^, Electro, Oi, Finland) for HR control and monitoring. To calculate the intensity of DWR-IT, the heart rate maxima (HRmax) will be recorded in the terrestrial environment by using the following equation: HRmax = 220 – age [29]. Next, the volunteers will remain immersed in the orthostatic position with water at the level of the sternum. After 5 min of rest, the HR will be measured. Afterwards, the immersion bradycardia (ΔHR), which in turn depends on the depth, temperature, and posture during the exercise, will be calculated [29]. The following formula HRmax - ΔHR will be applied to calculate the heart rate of volunteers in the aquatic environment, the following HRmax - ΔHR equation will be used [30]. During each DWR-IT session, the subjective perception of effort will be monitored and recorded [31].
First week: adaptation to a liquid environment and DWR-IT learning (44 min).Second and third week: warm-up of 2 min, then the exercise with an intensity of 60% to 65% of HRmax in the water, lasting 34 min. Two moments of sprints with 10 s for 30 s of rest (four series) were performed between the continuous exercises. After the training, 2 min of cool down was performed.Fourth to sixth week: the same procedures were performed as described in item b, but the continuous exercises lasted 33 min and five sprints were performed.Seventh to ninth week: the same procedures described in item b were performed, but the continuous exercises had an intensity of 66% to 70% of HRmax in the water, lasting 31 min. Three moments of sprints (four series) were performed among the continuous exercises.Tenth to twelfth week: the same procedures were performed as described in item b, but the continuous exercises had an intensity of 66% to 70% of the HRmax in the water, lasting 30 min, and three sprints (five series). Figure 3 shows the schematic diagram of the DWR-IT program.

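### Minor safety and dose point: stable users of any anti-hypertensive class are admitted, but the weeks 2–12 heart-rate band rests on 220 − age and would be too high for anyone on a heart-rate-lowering drug

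*Protocol article*

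**What the plan says.** Exclusion criteria: "For those who use anti-hypertensive drugs and hormone replacement therapy, a change in medication class or dose will not be allowed". This restricts changes during the study; it excludes no drug class at entry.

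Water group (intervention group): maximum heart rate is predicted "by using the following equation: HRmax = 220 – age", not measured. The immersion bradycardia (ΔHR) is then subtracted. It comes from a resting reading in the water: "After 5 min of rest, the HR will be measured". The target is a percentage of the result:

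- Weeks 2–3: "the exercise with an intensity of 60% to 65% of HRmax in the water, lasting 34 min". Weeks 4–6 keep this band with 33 min of continuous exercise.
- Weeks 7–9: "the continuous exercises had an intensity of 66% to 70% of HRmax in the water, lasting 31 min". Weeks 10–12 keep this band with 30 min.

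Week 1 and the sprints have no heart-rate target in the text. In each session "the subjective perception of effort will be monitored and recorded".

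Three other sections bear on the point. Baseline characteristics provides for collecting "details covering demographic data, lifestyle, medications, identification of other diseases". Inclusion criteria requires a medical document "attesting the absence of cardiovascular disease that is restrictive to practice the aquatic physical training". Intervention and follow-up periods limits groups to four volunteers with at least two therapists.

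**The concern.** The formula uses only age and a resting correction. It cannot respond to a drug that lowers the heart rate a participant can reach. The Exclusion criteria foresee anti-hypertensive users and require their class and dose to stay constant, so any such effect would last through the whole programme.

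For such a participant the written band asks for more effort than its percentage suggests. At stake are the safety of that participant and the fidelity of the dose. The Discussion faults earlier trials for poor control of aquatic exercise intensity and presents heart-rate prescription as a strength here. A rule that misfires for an admitted subgroup weakens that strength.

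**Working it through.** The plan gives no figure for this subgroup, so there is none to reproduce. The check is how the written rule behaves when true maximum heart rate is below 220 − age.

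**Inputs from the protocol article**
- Age 39 to 59 (Inclusion criteria), so 220 − age runs from 181 down to 161 bpm.
- Bands 60–65% (weeks 2–6) and 66–70% (weeks 7–12); three sessions a week.

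**Assumptions (no values in the article)**
- ΔHR: 10 bpm, with a range of 0 to 20.
- Drug-related fall in true maximum, r: 10 or 20 bpm, with 30 and 40 as extremes.

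**Formula.** Let H = 220 − age − ΔHR. The target at nominal share p is p × H. The true aquatic maximum is H − r. The actual share is p × H / (H − r), which equals p when r = 0 and exceeds p whenever r > 0.

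**Age 50, ΔHR = 10.** H = 220 − 50 − 10 = 160. The 60–65% band is 96–104 bpm and the 66–70% band is 105.6–112 bpm.

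| Assumed fall r | True maximum | Nominal 60–65% becomes | Nominal 66–70% becomes |
|---|---|---|---|
| 0 | 160 | 60–65% | 66–70% |
| 10 | 150 | 64.0–69.3% | 70.4–74.7% |
| 20 | 140 | 68.6–74.3% | 75.4–80.0% |
| 30 | 130 | 73.8–80.0% | 81.2–86.2% |
| 40 | 120 | 80.0–86.7% | 88.0–93.3% |

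**When the whole band lies above its own ceiling.** This needs r > H × (1 − lo/hi).
- 66–70%: 160 × (1 − 66/70) = 9.1 bpm.
- 60–65%: 160 × (1 − 60/65) = 12.3 bpm.

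Over ages 39–59 and ΔHR 0–20, H runs from 141 to 181. The thresholds are then 8.1–10.3 bpm and 10.8–13.9 bpm.

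**Sensitivity of the upper limit.** Over the same ranges, nominal 70% becomes 74.1–75.3% at r = 10 and 78.7–81.6% at r = 20. The result depends mainly on r. Subtracting ΔHR does not repair the error: it makes H smaller, which slightly raises H / (H − r) for a given r.

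**Exposure.** Weeks 2–3: 6 sessions × 34 min = 204. Weeks 4–6: 9 × 33 = 297. Weeks 7–9: 9 × 31 = 279. Weeks 10–12: 9 × 30 = 270. In total, 33 of 36 sessions and 1,050 min have a heart-rate target.

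**The case against.** The strongest reply is that this may concern nobody. The water group is planned at 15 people, declared cardiorespiratory disease is excluded, and a medical document is required. The article gives neither the number of users of such drugs nor the size of the drug effect. This stands, and it limits the weight of the point.

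A second reply is that the thresholds partly reflect narrow bands. At H = 160 the 66–70% band spans only 6.4 bpm, and an unmedicated person whose true maximum is 9 bpm below 220 − age has the same shift. That also stands: at r = 10 the shift is modest. The drug case differs in that its direction is known and the people can be identified from the medication list.

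A third is that practice may already cover it. Therapists are present, effort is recorded, and Fig. 3, whose content is not shown in the text, is described as giving weekly intensities. These lower the risk, and the figure should be checked. The running text, however, lets neither the medication list nor the effort rating alter the target. The medical document addresses disease, not drugs.

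A fourth is that a journal article condenses the full protocol. That would answer a complaint about missing detail. Here the admission rule, the formula and the percentages are all stated, and together they give the wrong target for an admitted subgroup.

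**Conclusion.** The point holds as a minor, conditional one. For a participant on a heart-rate-lowering drug, the stated 60–65% and 66–70% bands are larger shares of true maximum than intended. The direction follows from the formula. The size rests on assumed values: at age 50 with ΔHR of 10 bpm, a fall of 10 to 20 bpm turns 66–70% into about 70–80%.

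A reader might infer two stronger conclusions that the document does not support.

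- **That participants will be trained near their maximum.** The 88–93% row needs an assumed 40 bpm fall. The band is also a nominal target that a participant may not reach, and nothing shows that therapists would push someone towards an unattained rate.
- **That the trial's result is compromised.** No affected participant is shown, and the target applies only within the water group. Nothing here bears on between-arm bias, the sample size or the planned tests.

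**What to change.** Add to the Water group section a statement to this effect: participants whose baseline medication list shows a heart-rate-lowering drug train in weeks 2–12 to the moderate range of the perceived-effort scale already recorded each session, with the scale and range fixed in advance. For them the band based on 220 − age is neither a goal nor relied on as a safety ceiling; heart rate is still recorded.

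The band should not be kept as an upper limit for these participants, because it is the quantity that is too high for them: in the example, 112 bpm is already 80% of true maximum at r = 20. The running text names neither the scale nor a range, so the investigators must supply both from the scale in use.

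The cost is small: no new measurement and no change to eligibility or analysis. The downside is a less uniform dose for these few participants and a second dosing rule. Trial status reports that data collection is in progress, so the rule might reach people already training. Record the date of the change and the number of participants it applies to, even if that number is zero.

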### Randomization and allocation

Randomization will be performed after baseline assessments. Sequentially numbered opaque sealed envelopes will be prepared ahead of time and randomly assigned by a computer-generated table of random numbers in a 1:1 proportion. A person blinded to the study protocol will perform the randomization and provide the group assignment to the treating physical therapist. Volunteers will be allocated to the water group, which will be submitted to the 12-week DWR-IT program, or to the control group, which will not be submitted to intervention and will be instructed not to engage in any kind of structured physical exercise training and to keep the life activities identified at baseline. The International Physical Activity Questionnaire (IPAQ) will be applied before and after the intervention in order to assess the level of physical activity. Failure to follow the recommendations is an exclusion criterion in the study (Fig. 2).

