#### Intervention and follow-up periods

The intervention program will comprise 36 sessions, three times a week (in alternate days) during the morning, for 12 weeks, performed in a heated pool (32 °C). Sessions will be held in groups of no more than four volunteers and will be supervised by at least two therapists.

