#### Control group

The control group will not undergo any form of treatment. Volunteers will be instructed not to change their daily usual activities or diet or participate in other physical activities. During intervention, the volunteers will be monitored by phone calls from the researchers every week, and IPAQ and food frequency questionnaire (FFQ) will be used to monitor and control the level of physical activity and the frequency and quantity of food consumed; both will be applied before intervention, at week 6, and after the intervention period. If there are changes in dietary habits or level of physical activity, the volunteers will be excluded from the study.

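### After randomisation, poor attenders are dropped from the water group only and controls are dropped for any lifestyle change, so the analysed groups are not the randomised groups

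*Protocol article*

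**What the plan says.** - **Timing.** The protocol article (Randomization and allocation) places randomisation after the baseline assessments, so attendance and lifestyle change can be seen only afterwards.
- **Water group.** Exclusion criteria: "data from samples that did not obtain at least 80% frequency in the sessions will be excluded". Intervention and follow-up periods: "The intervention program will comprise 36 sessions". Controls have none: "The control group will not undergo any form of treatment".
- **Control group.** "If there are changes in dietary habits or level of physical activity, the volunteers will be excluded from the study". Randomization and allocation, after the instructions to controls and the sentence on the physical activity questionnaire (IPAQ), adds: "Failure to follow the recommendations is an exclusion criterion in the study".
- **Both arms.** Exclusion criteria also says that volunteers "may not participate in another training or nutritional monitoring program during the aquatic intervention", and does not allow a change in the class or dose of certain medicines. Neither sentence is limited to one arm.
- **IPAQ schedule.** One section says it "will be applied before and after the intervention in order to assess the level of physical activity". The Control group section says of the IPAQ and the food frequency questionnaire (FFQ) that "both will be applied before intervention, at week 6, and after the intervention period".
- **Who decides.** The Abstract calls the trial open. Under Availability of data and material, one researcher is responsible for assessment, reassessment and supervision of the intervention.
- **Analysis.** The section names the tests and the effect size measure. It does not say that all randomised participants are analysed as allocated.

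**The concern.** Randomisation protects the comparison only while the groups stay as they were formed. Here each arm is filtered on later behaviour, and by a different rule. People who miss more than a fifth of the sessions may be those who tolerate training least or gain least from it. Dropping them leaves a selected water group, and no matching filter can be applied to controls.

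Controls are filtered on lifestyle change. The activity part of that rule cannot be mirrored in the water group, whose assigned programme itself adds three sessions a week. What counts as a change is not defined, and the decision falls to staff who know the allocation. The number removed, and which people, is therefore discretionary.

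At stake is whether the walk-test result estimates the effect of being assigned to the programme, or compares good attenders with controls whose habits stayed the same. The rules are stated in the text, so neither the condensed format of the article nor a separate analysis plan accounts for them.

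**Working it through.** **1. The attendance cut-off.** 80% of 36 sessions is 0.8 × 36 = 28.8, so anyone attending fewer than 29 sessions is dropped.

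**2. The plan's own figures (Sample size).** The pilot walk distance was 566.2 ± 51.8 m before and 625.1 ± 73.6 m after, a difference of 58.9 m. The plan has 12 per group, raised for 20% dropout: 12 / (1 − 0.20) = 15, which reproduces.

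**3. SD of change.** The pre–post correlation r is not given.
SD = √(51.8² + 73.6² − 2·r·51.8·73.6)
- r = 0.5: 65.5 m
- r = 0.7: 52.6 m
- r = 0.3: 76.2 m

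I use r = 0.5 as an assumption. With it, a two-sided paired t test at 5% needs 12 participants for 80% power (power 0.809), the same number as in the plan.

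**4. Bias from removing 3 of 15.** Suppose there is no true effect, and that attendance has correlation ρ with the change in walk distance. The 12 largest of 15 standard normal values average 0.327, so dropping the 3 poorest attenders shifts the water-group mean by ρ × SD × 0.327:
- ρ = 0.3: 0.3 × 65.5 × 0.327 = 6.4 m
- ρ = 0.5: 0.5 × 65.5 × 0.327 = 10.7 m

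These are 11% and 18% of 58.9 m. Across the SD range the result runs from 0.3 × 52.6 × 0.327 = 5.2 m to 0.5 × 76.2 × 0.327 = 12.5 m.

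**5. Adding the control rule.** The text gives no direction, so three cases are shown, each removing 3 of 15 controls with the same ρ. Type I error comes from simulation, using a two-sided t test on change scores. With two time points this is the group-by-time test of the planned mixed ANOVA.

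| Removed from controls | ρ = 0.1 | ρ = 0.3 | ρ = 0.5 |
|---|---|---|---|
| None (attendance rule alone) | 2 m, 5.0% | 6.4 m, 5.8% | 10.7 m, 7.3% |
| Largest change in either direction | 2 m, 5.1% | 6.4 m, 5.8% | 10.7 m, 7.2% |
| Only those who became more active | 4 m, 5.2% | 12.9 m, 7.9% | 21.4 m, 13.6% |
| Only those who became less active | 0 m, 5.0% | 0 m, 5.3% | 0 m, 5.7% |

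At ρ = 0 the bias is 0 m and the error about 5% in every row. Analysing all 30 as allocated also gives about 0 m and 5%.

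**The case against.** The strongest reply is that the direction and size of the bias are not in the document. A reader might infer that both rules push the estimate towards the water group. The text does not support that. It speaks only of changes, so controls who eat worse or move less are removed too. If change in either direction counts equally, the control rule adds nothing to the attendance bias; if mainly worsening controls go, the two can cancel. The ban on structured exercise for controls makes removal of the more active plausible, but no more than that. This part of the reply stands, and so the third row of the table is an upper scenario.

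Two further inferences also go too far:

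- **That the analysed number must fall below 12 per arm because these exclusions use up the dropout allowance.** The Sample size section does not say what its 20% covers, and removing 3 of 15 leaves exactly 12.
- **That every exclusion differs by arm.** The bans on other programmes and on medication changes apply to all volunteers, and the medication sentence does not say that data are dropped.

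It can also be said that the week-6 questionnaires simply add to a before-and-after schedule. That is possible, but the two sections do not say so.

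None of this answers the central point. The attendance rule is explicit, acts after allocation and can touch only one arm.

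**Conclusion.** The point holds. As written, the plan does not compare the randomised groups. Poor attenders leave the water group by a rule that has no counterpart among controls, and controls leave by a rule without threshold or direction, applied in an open trial.

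The attendance rule is likely to favour the water group, by about 6 to 11 m with type I error of about 6–7%. The upper scenario, in which only controls who became more active are removed, is about 13 to 21 m (22–36% of the 58.9 m planning difference) and about 8–14%.

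These figures rest on assumptions: 3 of 15 removed, a pre–post correlation of 0.5 and an attendance–change correlation of 0.3 to 0.5. At 0.1 the bias is about 2 to 4 m with almost no inflation of error. The loss of the randomised comparison does not depend on these assumptions; only its size does.

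**What to change.** 1. Stop using two rules to remove randomised participants from the primary analysis: the 80% attendance rule (Exclusion criteria) and the control diet and activity rule (Control group, and its echo under Randomization and allocation).
2. State that every randomised participant is analysed in the allocated arm, whatever their attendance or lifestyle change.
3. Seek the week-12 assessment from everyone, including those who stop attending or change their habits.
4. Use an analysis that keeps participants with incomplete data, for example a mixed model. A conventional mixed-design ANOVA drops anyone without a week-12 value, so a change of wording alone would not be enough.
5. Report 80% attendance and lifestyle stability only as a labelled per-protocol sensitivity analysis, with change in diet and activity defined in advance.
6. Reconcile the two IPAQ schedules and apply one schedule in both arms.

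The cost is a change of wording, a different model and some extra follow-up visits. The estimate may be somewhat smaller than among good attenders. The trial is in data collection, so the change should be made soon: week-12 outcomes that are not collected cannot be recovered.
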